### Assignment of Interventions

#### Randomization

Couples will be randomly assigned to 1 of 2 conditions, CHTC retesting or individual rapid HIV testing. Randomization will be stratified for previous randomization in the 4Us trial (CHTC as usual, CHTC plus the substance use calendar, CHTC plus the ACT video, and CHTC plus both adjunct components). The random assignment will be performed by the project manager, who will enter the stratification criteria in Qualtrics to obtain the condition before intervention delivery.

#### Blinding

Intervention staff cannot be blinded to the condition they are delivering. Likewise, participants cannot be blinded to the condition. The 12-month follow-up in the 4Us trial (which serves as the preintervention data point for this study) is completed before participants are consented to this study. Assessment staff are blinded to condition at follow-up. Where blinding is possible, unblinding is not anticipated.

### Data Collection, Management, and Analyses

#### Data Collection for Primary Outcomes

##### Self-Reported Sexual Behavior

Procedures are the same as those used in the ongoing 4Us protocol [47]. Research assistants gather self-reported sexual behavior data for the past 30 days using a structured TLFB interview (Sobell and Sobell [53]). A Microsoft Access (Microsoft Corporation) database is used to facilitate the capture of data, including “anchor dates” or significant events; missed PrEP doses (for those on PrEP); heavy drinking and drug use; and sexual events. Sexual event data further comprise partner type (main or casual), the sex act performed (eg, anal insertive and anal receptive), and whether a condom was used.

##### Biological Testing

The Molecular Testing Laboratory (MTL) coordinates at-home STI testing. Materials necessary for collection and return shipping are delivered before the scheduled assessment meeting with the research assistant. Specimen collection is completed at a time designated in the assessment. The research assistant is available to review collection procedures, confirm the accuracy of shipping information, and observe the packaging of specimens for shipment.

The presence of urethral STIs will be tested in urine specimens; meanwhile, the presence of rectal STIs will be tested in (self-administered) rectal swab. The Abbott RealTime CT/NG assay is used to evaluate the presence of *Chlamydia trachomatis* and *Neisseria gonorrhoeae*. This is a Food and Drug Administration (FDA)–cleared real-time polymerase chain reaction assay for direct, qualitative detection of a region of the cryptic plasmid DNA of *C trachomatis* and the Opa gene of *N gonorrhoeae*.

##### HIV Testing

HIV testing, during CHTC and individual HIV testing sessions, will be performed using the Oraquick 4th generation testing kit. These kits are approved for at-home self-testing, and FDA-approved instructions are included. At follow-up (6 months), HIV testing will be conducted individually using self-administered dried bloodspot, giving participants the option of an Oraquick HIV to complete their HIV test if they prefer.

##### Retention Plan

Retention procedures continue those used in the ongoing 4Us trial [47], from which participants for this study are recruited. Assessments are conducted individually to retain participants who break up and whose relationship may have ended during the course of their participation in the study and to reduce the burden associated with coordinating a single assessment session with both partners. Study staff have at least quarterly contact with participants through email, SMS text messaging, and telephone (based on participant preference), which serves to maintain engagement and the accuracy of contact information over the study period.

#### Data Management

TLFB data are gathered by a trained interviewer using a data-entry system programmed in Microsoft Access. The institutional review board of Hunter College has reviewed all study procedures. In addition, procedures are reviewed by the Data Safety Monitoring Board (DSMB), which consists of experts in sexual health and substance use intervention research with SMM.

#### Data Analysis Plan

##### Data Screening Procedures and Analyses of Attrition

We will follow standard procedures for cleaning data and assess whether variables conform to the distributional assumptions of our analyses. The 12-month follow-up assessment in the parent study serves as prerandomization (ie, baseline) data for the purposes of these analyses. We will begin with a sensitivity analysis to examine whether couples enrolled into the randomized controlled trial proposed in this revision differ from those participants in the parent study (DA050508) who are not enrolled either due to relationship termination or lack of interest. This analysis will serve to identify behavioral factors (eg, drug use or sexual risk-taking) and relationship factors (eg, satisfaction, commitment, or communication skills) that are associated with relationship termination and uptake of CHTC retesting (among those couples who remain together). Subsequently, we will conduct an analysis of randomization success and attrition to determine if either is associated with (1) demographic variables or (2) drug use or TRB outcomes assessed at the 12-month 4Us follow-up. Factors that are observed to covary significantly with randomization or attrition will be incorporated in outcome analyses.

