##### Primary Analyses of Intervention Effects

The primary hypothesis is that CHTC retesting will be associated with significant reductions in sexual HIV TRB (primary) outcomes compared to individual HIV testing. Using procedures similar to our previously published studies [54], outcome analyses will be conducted in a multilevel modeling framework. Analyses will use full-information maximum likelihood estimation and specify a negative binomial distribution consistent with the count nature of primary outcomes. The appropriateness of a Poisson distribution will be determined by inspection of the significance of the dispersion parameter in negative binomial models. This accounts for the nesting of individuals within couple. Because randomization occurs at the couple level, condition is a level 2 variable. The effect of the intervention will be evaluated by examining the regression coefficient (and associated *P* value). Separate models will be calculated to predict outcomes at 3- and 6-month follow-ups (with Bonferroni correction for repeated nonorthogonal tests). Mplus (Muthén and Muthén) accommodates count and dichotomous outcomes within the multilevel modeling context. Analysis of secondary outcomes will follow analogous analytic procedures.

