## Discussion

The results of this trial have the potential to inform a previously unstudied aspect of CHTC—the utility of repeated, annual completion. This trial will be the first experimental evaluation of CHTC retesting. Results therefore have the potential to substantively inform CHTC guidance.

At the same time, several limitations arise as a function of study design. Both partners in a couple must consent to participate in resting. We are therefore unable to compare CHTC to a condition in which 1 (but not both) partner receives an individual HIV test. In addition, this trial is subject to the limitations of the 4Us study from which participants are recruited. Briefly, the demands of dyadic participation may present barriers to study enrollment or engagement, particularly for couples with relatively lower relationship quality [55]. The sample will not include partnered SMM in relationships where one partner is unable or unwilling to participate. The 4Us sample is recruited through advertisements on social networking and dating applications. It, therefore, underrepresents SMM who do not engage in these digital spaces. Furthermore, all participants in the 4Us study are aged 17 years or older, and at least 1 partner must be aged 17-29 years. This limits the generalizability of findings to adolescents and older adults.

Despite these limitations, this study has the potential to enhance knowledge about the effects of CHTC on the sexual health of SMM couples. This may inform future efforts to disseminate the intervention in the United States and internationally, as well as to gender-diverse couples.

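### The attrition screen leaves out the relationship measures the plan already names, so dropout tied to relationship quality differently in the two arms would be only partly adjusted for

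*Protocol article*

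**What the plan says.** Under Data Screening Procedures and Analyses of Attrition, the article plans two analyses.

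- **Enrolled against not enrolled.** Parent-trial participants who enter this trial are compared with those who do not. The candidate correlates include behavioral factors and "relationship factors (eg, satisfaction, commitment, or communication skills) that are associated with relationship termination and uptake of CHTC retesting".
- **Randomization success and attrition.** This analysis is to "determine if either is associated with (1) demographic variables or (2) drug use or TRB outcomes assessed at the 12-month 4Us follow-up". Relationship factors are not listed here, and condition is not listed as a correlate of attrition.

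The adjustment rule follows: "Factors that are observed to covary significantly with randomization or attrition will be incorporated in outcome analyses".

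Primary Analyses of Intervention Effects adds three facts. "Analyses will use full-information maximum likelihood estimation". Models at 3 and 6 months are separate. Condition is in the outcome models: "Because randomization occurs at the couple level, condition is a level 2 variable".

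Two other sections bear on dropout. The Discussion says that "the demands of dyadic participation may present barriers to study enrollment or engagement, particularly for couples with relatively lower relationship quality". The Retention Plan has partners assessed individually, in order to "retain participants who break up and whose relationship may have ended during the course of their participation".

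**The concern.** The investigators hold the relationship measures and treat them as relevant to who enters the trial. They do not use them for who is lost from it, and loss after randomization is what can disturb the randomized comparison. The Introduction, citing interdependence theory, says that partners coordinate prevention more easily when the relationship functions well. The same factor could therefore plausibly affect both follow-up and TRB.

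The two sessions also differ in a way that could matter. The CHTC session covers the couple's relationship and sexual agreement jointly, while the individual session steers away from the partner. If weaker couples are lost more often after one session than after the other, and if they have more TRB, the arm that loses them looks better than it is.

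Full-information maximum likelihood does not remove this by itself. With a separate model at each time point and no relationship covariate or auxiliary variable named, a couple with neither partner's outcome at that visit contributes no outcome information. The estimate then depends on the covariates that the screen happens to admit.

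**Working it through.** The article states no attrition figure, so there is none to reproduce. Two checks were made on the count outcome. Every dropout rate, risk ratio and share below is an assumption.

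**1. Hand calculation, no true effect, no adjustment.** Let p be the share of low-quality couples and RR their TRB rate relative to other couples. Dropout in the individual-testing arm is 10% for everyone. In the CHTC arm it is d for low-quality couples and 10% for the rest. Among completers the low-quality share is

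- CHTC arm: t = p(1 − d) / [p(1 − d) + (1 − p)(0.90)]
- individual-testing arm: c = p

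and the observed rate ratio is [1 + (RR − 1)t] / [1 + (RR − 1)c].

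| p | d | t | Ratio, RR = 2 | Ratio, RR = 3 |
|---|---|---|---|---|
| 0.4 | 0.30 | 0.28/0.82 = 0.341 | 1.341/1.4 = 0.958 | 1.683/1.8 = 0.935 |
| 0.3 | 0.30 | 0.21/0.84 = 0.250 | 1.25/1.3 = 0.962 | 1.50/1.6 = 0.938 |
| 0.4 | 0.20 | 0.32/0.86 = 0.372 | 1.372/1.4 = 0.980 | 1.744/1.8 = 0.969 |
| 0.3 | 0.20 | 0.24/0.87 = 0.276 | 1.276/1.3 = 0.981 | 1.552/1.6 = 0.970 |

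The spurious reduction is about 4% to 6.5% with 30% dropout and 2% to 3% with 20%. Against the 20% reduction in the Sample Size section, the whole range is about a tenth (2/20) to a third (6.5/20).

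**2. Simulation, true rate ratio 0.80.** There were 400,000 units with one count each. The mean rate was 2, the log rate fell by 0.4 per standard deviation of relationship quality, and there was further log-normal variation (SD 0.5). The baseline count stands for 12-month TRB. Poisson models were fitted to completers.

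| Dropout depends on | Dropout, individual / CHTC | Condition only | + 12-month TRB | + TRB and relationship quality |
|---|---|---|---|---|
| Arm only | 9.9% / 24.9% | 0.799 | 0.800 | 0.800 |
| Quality, equally in both arms | 22.7% / 22.7% | 0.802 | 0.804 | 0.804 |
| Quality, CHTC arm only | 15.1% / 17.6% | 0.757 | 0.776 | 0.802 |
| Quality, more strongly in CHTC arm | 20.4% / 24.0% | 0.745 | 0.766 | 0.797 |

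The first two rows show no material bias. In the last two, the unadjusted estimate is low by 1 − 0.757/0.80 = 5.4% and 1 − 0.745/0.80 = 6.9%, close to the upper end of the hand calculation. Adding 12-month TRB closes (0.776 − 0.757)/(0.80 − 0.757) = 44% and (0.766 − 0.745)/(0.80 − 0.745) = 38% of the gap. Adding relationship quality closes essentially all of it.

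In the last two rows overall dropout differs between arms by only 2.5 and 3.6 percentage points. A comparison of dropout counts by arm could easily miss this pattern, which is why the interaction is the informative test.

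**The case against.** A reader might infer that dropout driven by arm is left unadjusted, or that the trial will never compare attrition between arms. The document supports neither reading. Condition is in every outcome model, and arm-only dropout left the simulated ratio at its true value. Dropout counts by arm are routine reporting that a condensed article may leave to the full plan, so silence does not show that they are omitted.

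A reader might also infer that any dropout related to relationship quality biases the result unless quality is in the model. For the rate ratio that is too broad: with equal dependence in both arms the simulation showed no bias, given an intervention effect that is constant across levels of quality.

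Three further objections have weight.

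- The Discussion speaks of enrollment or engagement, among limitations inherited from the parent trial. It does not say that relationship quality causes missing 3- or 6-month data. Nothing in the article predicts that such loss would differ by arm.
- Individual assessment reduces loss after a break-up. Enrolled couples are also already selected: still together, 12-month follow-up complete, and both partners consenting.
- 12-month TRB is in the screen and is a partial proxy for relationship quality, so the plan may correct some of the bias.

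These points lower the likely size. They do not close the gap: TRB enters only if it is significant in the screen, and it removed less than half of the simulated bias. Using different variables for enrollment and for attrition is not a contradiction, but the attrition list and its adjustment rule are stated choices that can be improved.

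**Conclusion.** The point holds in a narrow form. The stated screen cannot bring relationship factors into the outcome models, although the plan already names them. This matters when dropout depends on relationship quality differently by arm and relationship quality also predicts TRB.

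Under the assumed inputs (30% to 40% low-quality couples, two to three times the TRB rate, 20% or 30% against 10% dropout), the unadjusted rate ratio shifts by roughly 2% to 6.5%. Less would remain if 12-month TRB entered the model. In the examples the shift favors CHTC because the extra loss was placed in that arm; extra loss in the other arm would reverse it. The article has no data to say whether this pattern will occur or how large it would be.

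This is a cheap improvement to a stated rule. It does not show that the planned analysis is invalid.

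**What to change.** Under Data Screening Procedures and Analyses of Attrition, extend the attrition analysis. Test missingness at 3 and at 6 months against condition, demographics, 12-month drug use and TRB, the 12-month relationship measures, and the interaction of condition with those measures.

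Under Primary Analyses of Intervention Effects, pre-specify one 12-month relationship-quality score as a covariate or auxiliary variable in the outcome models, whatever its significance in the screen. Fixing it in advance matters because a significance screen may miss a modest but influential predictor.

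The cost is plan wording and one or two extra model terms. The measures are ones the plan already intends to analyze, so no new data collection should be needed.

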### Sample Size

Power to detect significant between-group differences in primary outcomes was calculated using the PASS program (version 2022; NCSS, LLC). Analyses focused on power to detect a significant between-group difference at any 1 follow-up time point. Results from the tests for difference between 2 Poisson rates in a cluster randomized design module indicated the study had power of >0.80 to detect a 20% or greater reduction in the rate of CAS with casual partners. This estimate assumed a sample of 200 couples with equal allocation to condition, and models were tested with based rates of 2-4 instances of CAS with a casual partner among the control (individual HIV testing and counseling) condition. Results from the tests for 2 proportions in a cluster-randomized design suggested proposed study has power of >0.80 to detect a 22% reduction in the proportion of reporting main partner TRB, assuming a sample of 200 couples and a 70% base rate in the control condition.

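### Covariates for the outcome models are chosen partly by significant association with randomized arm, so the 12-month baseline outcome will rarely enter by that route and the 4Us stratum almost never

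*Protocol article*

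**What the plan says.** Under *Data Screening Procedures and Analyses of Attrition*, the article sets the baseline: "The 12-month follow-up assessment in the parent study serves as prerandomization (ie, baseline) data for the purposes of these analyses". It then plans an analysis of randomization success and attrition. The factors tested are demographic variables and the drug use and transmission-risk outcomes at that 12-month visit. The result feeds the models: "Factors that are observed to covary significantly with randomization or attrition will be incorporated in outcome analyses".

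Under *Randomization*: "Randomization will be stratified for previous randomization in the 4Us trial", with four 4Us conditions.

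Under *Primary Analyses of Intervention Effects*, the model is a multilevel count model with separate fits at 3 and 6 months. The only term named is the treatment: "Because randomization occurs at the couple level, condition is a level 2 variable". Neither the 12-month outcome nor the 4Us condition is named as a covariate, and neither is ruled out. The 4Us components reappear only in the preliminary analysis under *Moderation or Mediation Analyses*.

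**The concern.** The rule has two halves. The attrition half has a rationale. The randomization half does not: if assignment was carried out properly, a significant difference between arms before treatment is a chance event, and its P value does not measure how strongly the factor predicts the outcome.

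Three things follow.

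- The pre-randomization value of the outcome, usually among the best predictors available, is only a candidate. By this route it enters only when chance has made the arms differ.
- The 4Us condition is not on the stated list of tested factors. Even if it were tested, stratification is meant to balance it, so the test would almost never select it.
- The covariate set is not known until the data are in. If the second primary outcome is modelled as a proportion with a logit link (the link is an assumption; the *Sample Size* section powers it as a proportion), the odds ratio also changes meaning with the covariates included.

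At stake is precision, in a trial planned for 200 couples that had enrolled 53 by February 2024.

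**Working it through.** **1. The plan's own power figure.** *Sample Size* states: "This estimate assumed a sample of 200 couples with equal allocation to condition". That is 100 couples, or 200 men, per arm. For outcome 1 it claims "power of >0.80 to detect a 20% or greater reduction in the rate of CAS with casual partners", and "models were tested with based rates of 2-4 instances of CAS with a casual partner" in the control arm. For outcome 2 it claims "power of >0.80 to detect a 22% reduction in the proportion of reporting main partner TRB", from a 70% base rate. Neither alpha nor the within-couple correlation (ICC) is given, so both are assumed here.

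Effective n per arm = 200/(1 + ICC). For outcome 1, power = Φ[(λ1 − λ2)/√((λ1 + λ2)/n) − z].

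- Rates 2 v 1.6, ICC 0, two-sided 0.05: 0.4/√(3.6/200) = 2.98; 2.98 − 1.96 = 1.02; power 0.846. With ICC 0.1 it is 0.811, and with ICC 0.2 it is 0.777.
- Rates 4 v 3.2: 0.846 to 0.988 at any ICC.
- Outcome 2, 70% v 48% (22% read as absolute): 0.89 to 0.995 at any ICC. Read as relative (0.70 × 0.78 = 54.6%): 0.83 at ICC 0.2 and 0.74 at ICC 0.5.

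The stated >0.80 is therefore consistent with alpha 0.05 under some of these assumptions, but cannot be reproduced uniquely. At 0.025 (an assumed 0.05 split over two time points), rate 2 gives 0.77 even at ICC 0.

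**2. Closed-form guide to what adjustment is worth.** In a linear model, adjusting for a baseline with correlation r multiplies the variance by 1 − r². A test with 80% power at two-sided 0.05 then has power Φ[2.80/√(1 − r²) − 1.96]:

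- r = 0.3: 2.80/0.954 = 2.94, power 0.84
- r = 0.5: 2.80/0.866 = 3.24, power 0.90
- r = 0.7: 2.80/0.714 = 3.92, power 0.975

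This is only a guide, because the outcomes here are clustered counts and a proportion.

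**3. Simulation of the rule itself.** There were 2,000 trials per scenario: 200 couples, stratified over four strata, overdispersed counts with mean 3, log-scale SD 1 and ICC 0.4, rate ratio 0.7, per-test alpha 0.025. Log-linear models with couple-robust standard errors stood in for the multilevel negative binomial model. Apart from the 200 couples and four strata, these settings are assumptions. The mean of 3 lies inside the plan's 2 to 4. Under the rule, the baseline outcome entered only if the arms differed at P<.05. The attrition route was not simulated.

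| Latent correlation | Stratum SD (log scale) | Power, rule | Power, fixed covariates | Gain (points) | SD of estimate, rule → fixed |
|---|---|---|---|---|---|
| 0.3 | 0 | 50.5% | 51.9% (baseline) | 1.4 | 0.164 → 0.161 |
| 0.5 | 0 | 53.3% | 57.4% (baseline) | 4.1 | 0.163 → 0.155 |
| 0.7 | 0 | 53.3% | 67.9% (baseline) | 14.6 | 0.156 → 0.137 |
| 0.5 | 0.3 | 46.2% | 54.8% (baseline + stratum) | 8.6 | 0.162 → 0.154 |
| 0.5 | 0.6 | 35.9% | 50.4% (baseline + stratum) | 14.5 | 0.176 → 0.167 |

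With no treatment effect, the baseline outcome entered in about 4 to 6% of trials, so the rule behaved almost like no adjustment. At the plan's own 20% reduction (correlation 0.5, no stratum effect) power was 21.4% under the rule and 24.1% with the baseline fixed.

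The last column does not depend on the size of the test. Squaring the ratios, for example (0.161/0.164)² = 0.96 and (0.137/0.156)² = 0.77, gives variance reductions of about 4% to 23%. The larger power gains are somewhat flattered: in the matching null runs the fixed-covariate tests rejected in 0.022 to 0.037 of trials against a nominal 0.025.

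**4. Bias, standard errors and type I error under the rule.** The average rate ratio was 0.997 to 1.005 where the truth was 1. Type I error at nominal 0.025 ran from 0.017 to 0.029. At correlation 0.5 with no treatment effect, mean standard error against true SD was 0.154 v 0.153 (no stratum effect), 0.164 v 0.161 (moderate) and 0.188 v 0.179 (strong). The last is 0.188/0.179 = 1.05, or 5% too wide; the matching run with a treatment effect gave 0.190/0.176 = 1.08.

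**The case against.** The strongest reply is that this is a condensed article whose analysis plan is not shown. Full covariate lists, stratification factors included, are commonly left to that plan, and the primary-analysis section points to procedures in earlier published studies. That stands as far as it goes: the missing stratum term on its own would be silence, not a fault. It does not protect the selection rule, which the article states outright.

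A reader might infer that the model leaves out the pre-randomization outcome. The article does not say so. The 12-month transmission-risk outcomes are named candidates. They can enter if the arms differ, or through the attrition half of the rule, and how often the attrition route would admit them was not examined.

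A reader might also infer that the confidence intervals would be wrong or false positives inflated. The simulations do not support this. The standard-error discrepancy attributable to ignoring the strata is small, appears clearly only when strata differ strongly, and makes the test conservative. No effect of 4Us condition on risk behavior is documented.

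Finally, predictors of attrition have a defensible place in models fitted by full-information maximum likelihood, since missing-at-random handling depends on what each model conditions on. That stands, so the criticism is confined to the randomization half.

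**Conclusion.** The point holds in a limited form. Significant association with arm is a poor rule for choosing covariates, and the article fixes it in writing. By that route the 12-month outcome will rarely enter and the 4Us stratum almost never; the latter assumes that allocation within strata is restricted enough to balance it. Nothing else in the article guarantees either term.

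The consequence is lost precision and a model that depends on the data. The simulated power loss is about 1 to 15 percentage points. It rests on assumed correlations of 0.3 to 0.7, assumed stratum effects, dispersion and ICC, a rate ratio of 0.7 that is larger than the planned effect, and a stand-in model. The closed-form gains are more optimistic at the lower correlations and should not be quoted as the expected benefit. Nothing here shows bias or an inflated type I error, and any standard-error error from ignoring the strata is small (about 5% in the null runs) and conservative.

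**What to change.** State in advance that every primary model, at 3 and at 6 months, includes (a) the participant's own 12-month 4Us value of that outcome and (b) the 4Us condition used as the stratum. Remove significant association with randomization as a route into the model; baseline comparability can still be described. Predictors of attrition may stay in the outcome models, but should be listed in advance, not chosen by significance tests after the data are in.

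If the unseen analysis plan already does this, the article's sentence only needs aligning with it. The cost is wording: the 12-month visit is an eligibility requirement and the 4Us condition is known before randomization, so no new data are needed. This is a free improvement.
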